#### B. (f)MRI measurements; Total duration ~ 45 min + 15–30 min. of installation/preparation

Grey matter volume assessment [139] (MP2RAGE (Magnetization-Prepared 2 Rapid Acquisition Gradient Echoes)—8 min.White matter assessment, allowing to compute i.a. Fractional Anisotropy (FA) for evaluating white matter integrity reflecting structural connectivity [140] (Diffusion Tensor Imaging, DTI)—7 min.Resting-state functional MRI, allows to measure activity in the Default Mode Network (DMN) reflecting global functional connectivity of the brain [141]; (Echo-planar imaging, EPI)—10 min.Task-related brain activity (task-fMRI). Letter n-back visual working memory task (2- (EPI)—15–20 min. (see fMRI n-back visual working memory task below).

The MRI measurements do not require any special preparation (such as having to drink or be injected with contrast materials or radioactive dye). Acquisitions are performed on a 3 T (Tesla) whole body Siemens Trio system (Siemens TIM-TRIO, Erlangen, Germany) in Geneva and on a 3 T whole body Siemens Prisma scanner (Siemens Prisma, Erlangen, Germany) in Lausanne.

We adapted the default sequences' parameters, opting for a compromise between a good signal-to-noise ratio and a minimum amount of time. The Siemens MRI protocols are optimally synchronized between the TRIO and PRISMA scanners at both sites. For the functional acquisitions, we adopted a multiband echo planar imaging fMRI with an accelerator factor of 3, allowing to reduce the repetition time to 1.350 s, which represents a good temporal resolution for fMRI (see Supplementary Table 3). Following these choices, we could reduce the total duration of the MRI scanning to 45 min, which is important in the context of our MCI patient population.

A detailed list of the different MRI measurements (*n* = 4) and main protocol parameters are provided in Supplementary Table 3.

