### Design, interventions and setting

### Study design

The proposed study is a 1) block-randomized, 2) 3-arm, 3) multicentric (HUG^3^, Genève; CHUV^4^, Lausanne), 4) national (Switzerland), 5) intervention study.

Blocked randomization is applied to the experimental groups only, blocking for the factors 1) age, 2) gender, 3) COGTEL weighted score [80] and 4) MCI diagnosis (1. amnestic; 2. non-amnestic) to balance both intervention groups for those factors. Experts at the memory clinics will select MCI diagnosed patients for participation.

We use a three-arm design: 2 experimental groups of MCI patients, and one matched passive healthy control group. Except at the level of statistical analyses, no blinding is applied.

The blocked (or stratified) randomization procedure is performed at each site separately, aiming to achieve an equal number of music and psychomotor groups at each site, using Ward’s Hierarchical Agglomerative Clustering Method [126]. We will use this method to establish duplets that are maximally similar with respect to the 4 blocking factors, based on minimum Euclidean distance. Subsequently, an algorithm will attribute randomly one participant of each duplet to each experimental group. So, half of the participants will end up in the music practice intervention (n ~ 16), and the other half in the psychomotor intervention (n ~ 16). A control group of matched (age, gender, education level) healthy controls (n ~ 16) that are not part of the randomization process, will be recruited in Geneva, and will receive financial compensation (gift vouchers).

In the documentation that we will provide to the patients we mention that there are 2 different intervention groups that we want to compare for their effectiveness to improve cognitive and motor function, and that for scientific reasons the repartition to the groups will be determined by chance. We will also mention that if patients refuse to accept their group allocation, they cannot participate in the study.

The psychometric battery consists exclusively of validated tests. Cognitive screening at the HUG and the CHUV is similar. The HUG uses the MMSE score [64] and the Hospital Anxiety and Depression Scale (HADS) [127]. At the CHUV the test used for general cognition is the Montreal Cognitive Assessment (MoCA) [128, 129]; they also use the HADS.

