### Setting

For Geneva participants, music interventions and passage of the behavioral test battery take place at the Geneva School of Health Sciences (Haute Ecole de santé de Genève (HEdS-GE) of the University of Applied Sciences and Arts Western Switzerland (HES-SO)). The psychomotor training takes place at the Department of Psychomotricity (Haute école de travail social de Genève, HETS-GE) of the University of Applied Sciences and Arts Western Switzerland HES-SO, Geneva School of Social work. Brain imaging (MRI) is performed at the BBL, the Brain and Behaviour Laboratory at the University Medical Center of the Geneva University.

For Lausanne participants, all interventions and passage of the behavioral test battery take place at the Leenaards Memory Center of the CHUV, and brain imaging (MRI) will be performed at the Laboratoire de recherche en neuroimagerie (LREN; Laboratory for Research in Neuroimaging) in the same building, also at the CHUV.

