### Recruitment, practical details

The recruitment should have started for the first wave of patients in May 2020. Finally, the COVID-19 epidemic caused a 4–5 months delay in the original schedule, and we started recruitment in September 2020 lasting till November 2020.

Mainly because of the anxiogenic and restrictive context of COVID-19, but also for personal reasons (too much time involved, etc.), most patients that seemed to fulfil the criteria initially contacted by the MC-HUG finally chose not to participate. In the end, only 14 patients that met all criteria consented to participate, and of those 4 more interrupted their participation, 2 who went into early dementia, one quit for health reasons and a last individual for personal reasons. Ten patients followed the interventions and passed the measurements, which is not enough for valid analyses (see the section Statistical power of the study).

Therefore, we recruited a second wave of patients at the LMC-CHUV, participating in the study from November 2021 to July 2022 (prescreening, interventions, and all measurements), and a third wave participating between July 2022 and April 2023. We intend to recruit enough patients to bring the total to 16 for both experimental groups. Baseline measures (t0) for the second wave started in December 2021, and for the third wave from August 2022, after the inclusion process (pre-screening and first visit).

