### Recruitment and procedure for the passive control group

Healthy passive controls will be recruited in the Geneva area among community-dwelling elderly from February 2022, through advertisements in local (elderly) journals, elderly centers (flyers, posters), and on the internet (i.a. www.planetesante.ch), once the recruitment of the experimental groups is over, to allow matching with the experimental groups.

Participants will be informed about the study's aims and the role of a control group and must, in principle, consent to pass all 3 measurement points (t0, t1, t2). Except for the MCI diagnosis, the same inclusion/exclusion criteria apply to this group as to the experimental groups. They will receive financial compensation by means of gift vouchers. We will first recruit a larger pool than necessary, to allow matching to the patient group.

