### Advanced multivariate statistical analyses

Finally, we will perform an exploratory analysis of the data using a multivariate data-driven approach. Analyzing separately behavioral data and several kinds of brain imaging data, cross-sectionally or over time, provides valuable information on these specific data. Additionally, combining diverse behavioral and different kinds of brain data within data-driven multivariate analyses may unravel hidden "covert" relationships [145, 146]. Specifically, we will perform multivariate data-driven analyses using multimodal Independent Component Analysis (ICA) [145, 146] and Partial Least of Squares (PLS) [147, 148] which have both been used successfully on multimodal brain imaging data.

Two methods will be used:

1) Joint, fusion, and linked ICA [149, 150] represent several blends of multimodal extensions of ICA that allow combining different types of data such as functional and structural neuroimaging data. The results of these analyses should reveal interactions between different types of information and consequently allow us to investigate differences between our groups / experimental conditions (interventions) [145, 149]. In addition, we will also decompose the fMRI data into functional brain networks using innovation-driven co-activation patterns (iCAPs), a recent approach of dynamic functional connectivity [151] that that can quantify temporal interactions between different networks.

2) PLS is another powerful technique that can identify components of multivariate relationships between imaging and behavioral data [148, 152], notably unified PLS correlation models [148]. This PLS technique allows revealing hidden relationships between all battery tests and MRI measurements over time and potentially show whether these relationships differ between the groups (machine-learning). We will also use PLS regression models to fit the best interventional neurobehavioral model for predicting the rehabilitation of elderly on a specific behavioral outcome i.e. evolution of the working memory performance. Implementations of these approaches are publicly available in addition to several in-house extensions that allow using them in the most flexible way, including machine-learning approaches [153, 154].

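### All controls are recruited in Geneva (Trio), while at least the wave 2 patients are tested and scanned in Lausanne (Prisma), so patient-versus-control imaging contrasts are partly confounded with scanner

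*Protocol article*

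**What the plan says.** - **Controls.** Under Study design, the matched healthy controls are people "that are not part of the randomization process, will be recruited in Geneva". The section on recruitment of the passive control group repeats this: "Healthy passive controls will be recruited in the Geneva area among community-dwelling elderly". They are matched to patients on age, gender and education level. Site is not a matching factor.
- **Patients.** Under Recruitment, practical details, wave 1 was approached through the Geneva memory centre, and "Ten patients followed the interventions and passed the measurements". After that, "we recruited a second wave of patients at the LMC-CHUV". A third wave follows, with no site named for it.
- **Where they are measured.** Under Setting, Geneva participants are tested and scanned in Geneva. "For Lausanne participants, all interventions and passage of the behavioral test battery take place at the Leenaards Memory Center of the CHUV", and their MRI is done in the same building.
- **Scanners.** Section B, (f)MRI measurements, gives a 3 T Trio "in Geneva and on a 3 T whole body Siemens Prisma scanner (Siemens Prisma, Erlangen, Germany) in Lausanne", with acquisition protocols synchronised between the two machines.
- **Analysis.** Comparisons and Basic statistical analyses plan to compare change over time in each patient arm with change in controls, and the two arms with each other. Baseline scores go into the models and demographic data may be added. Neither site nor scanner is named.
- **Randomisation.** It is done separately at each site and covers patients only.

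**The concern.** The controls are there to show what ageing and repeated testing do without an intervention. That works only if they are measured as the patients are. Lausanne has patients in both arms but no controls, so scanner, testing venue and, largely, recruitment wave are aligned with patient status. Synchronised sequences reduce differences between two scanner models but do not make the hardware the same.

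The primary outcome and all the secondary hypotheses are framed against the controls. For the imaging outcomes, a Prisma-versus-Trio difference could be reported as training-induced plasticity. A statistical analysis plan that is not shown could add a site term, but it could not supply Lausanne controls. The single-city control group is fixed by this document.

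**Working it through.** The plan gives no figure on site. Its sample size does reproduce: f = √(0.296/0.704) = 0.648, and a noncentral F for the two-group by two-time interaction with λ = f²(N − 2) gives N = 24, which is the stated 12 per group. This f corresponds to d = 2f ≈ 1.3, used in step 4.

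**Inputs from the article:** 16 per group; 10 wave 1 completers, taken as Geneva patients; minimum 12 per patient arm; two-sided alpha 0.05; controls in Geneva only. **Assumed, because the article gives no value:** scanner offset 0.5 SD; correlation r of baseline with follow-up 0.5–0.85; site-by-time effect 0.3–0.5 SD of change; equal split of arms within site.

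**1. Lausanne share.** If every patient after wave 1 is from Lausanne: (32 − 10)/32 = 22/32 = 69%, or (24 − 10)/24 = 14/24 = 58% at the minimum size. Controls: 0/16. These are upper bounds, because wave 3 may include Geneva.

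**2. Constant scanner offset δ, one arm versus controls.**
- Change scores: bias 0.
- Baseline as covariate: bias ≈ share × δ × (1 − r). With 0.6875 and δ = 0.5 this is 0.17, 0.10 and 0.05 SD for r = 0.5, 0.7 and 0.85.
- Type I error, simulated with 16 patients (11 in Lausanne) and 16 controls: 8.8%, 7.3% and 6.6% in 2,000 trials, hence about 7–9%. With 40,000 trials, which is more exact: 7.6%, 6.5% and 5.7%. At the highest r the excess over 5% is slight.

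**3. Site-by-time effect γ, in SD of change.** Bias = share × γ = 0.6875 × 0.3 to 0.6875 × 0.5 = 0.21 to 0.34 SD. The planned comparison is each arm against controls, so SE = √(1/16 + 1/16) = 0.354. The two-sided normal rejection rate is 9.0% to 16.3%. If only 11 of 32 patients were in Lausanne, the bias would be 0.10–0.17 SD and the rate 6–8%.

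**4. Cost of a site term.** With 5 Geneva and 11 Lausanne patients per arm, the site difference is estimated within the two arms with variance (1/5 + 1/11)/2 = 0.1455 (residual variance 1). Arm minus control then has variance 1/16 + 1/16 + (11/16)² × 0.1455 = 0.194, against 0.125 without the term. The ratio is 1.55 and the SE ratio 1.25.
- Power at d = 0.8: 0.60 falls to 0.43. At d = 1.3: 0.95 falls to 0.82.
- At 12 per patient arm the ratio is 1.40. If wave 3 restored a 16/16 site split it would be 1.25.
- Music versus psychomotor: variance 0.125 with or without the term.

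**5. Geneva-only comparison.** One arm (5) against 16 controls: variance 1/5 + 1/16 = 0.2625, SE 0.51. Both arms pooled (10): 1/10 + 1/16 = 0.1625. This is unconfounded by site but imprecise.

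**The case against.** The strongest reply is that the planned contrasts concern change, with baseline in the model. A reader might infer that scanner effects enter every patient-versus-control contrast. The documents do not support that: a constant offset vanishes from change scores and is mostly removed by baseline adjustment, and COGTEL and the questionnaires involve no scanner. For behavioural outcomes only a site effect such as setting or assessor could matter, and the article gives no evidence of one.

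Two further readings are tempting and also fail.
- That all later patients come from Lausanne. Only wave 2 is placed there, and both memory clinics are named as recruiting.
- That the pooled ICA and PLS analyses are cross-sectional and so carry the whole offset. The words "Analyzing separately behavioral data and several kinds of brain imaging data, cross-sectionally or over time" belong to a general remark on analysing data types one at a time. The PLS analysis is described as covering measurements over time, and this whole block is labelled exploratory.

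It is also fair that a site covariate is a detail commonly left to an analysis plan, and that the mixed models as described could accommodate one. Healthy, non-randomised controls already differ from patients by diagnosis, so site adds to an existing limitation.

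What stands is the design element itself: no Lausanne controls, two scanner models, and matching that omits site. Baseline adjustment does not fully remove an offset, nothing in the stated plan removes a site-by-time effect, and ICA or PLS group differences are exposed if scanner is ignored.

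**Conclusion.** The point holds in limited form. Imaging contrasts of patients with controls are partly confounded with scanner, with at most 69% of patients and no controls on the Prisma. The residual bias is small for a constant offset under baseline adjustment (0.05–0.17 SD for an assumed 0.5 SD). It is larger for a site-by-time difference (0.21–0.34 SD for an assumed 0.3–0.5 SD of change, with 9–16% false positives per arm). These sizes rest on assumed effects and on the upper-bound Lausanne share, and they shrink if wave 3 includes Geneva. Behavioural outcomes are exposed only to site effects, and the randomised music-versus-psychomotor contrast is not affected. This is a worthwhile and cheap correction to the analysis, not a defect that invalidates the trial.

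**What to change.** 1. Include site (scanner) and, where estimable, site-by-time in the patient-versus-control models, above all for MRI.
2. Beside each control contrast, report the Geneva-only patient-versus-control result as a sensitivity analysis.
3. In ICA and PLS, adjust for scanner or run within site, and do not interpret components that separate the scanners.
4. State the site of wave 3.

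These need wording only, with no extra participants or scans. The price is precision, as shown in step 4 of the working. There is also a limit of interpretation: with all controls in Geneva, the site term is estimated from treated patients alone and is largely aliased with wave. It can therefore absorb real differences in delivery or response between sites. Control-based imaging conclusions should be stated with that limit.

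Testing some of the same 16 controls in Lausanne, in the patients' proportion, would avoid the precision loss. It is worthwhile only if still feasible, since the article schedules control testing from March to October 2022.

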### fMRI n-back visual working memory task

This task is an alternation between 2-back, 1-back and 0-back working memory blocks of trials using uppercase letters. We adapted it from the design developed by Migo et al. 2015 [92], a neuroimaging study conducted on amnestic MCI patients. Blocked designs are optimal for short sessions because they are associated with high activation detection power [142, 143]. This task is simple, validated and widely used in psychology, moreover, MCI patients performed it successfully [92], thus ensuring the feasibility of the task allowing comparison with the literature. Yet, we will perform a behavioral training before the fMRI session, to ensure comprehension.

Letters will appear in series in the center of the screen. Patients are instructed to identify target letters under 3 conditions associated with an increasing load of working memory (see Fig. 1 for a complete description of the task and its paradigm). The 0-back condition is the baseline condition: patients compare the letters scrolling on the screen with one single target letter. In the 1-back condition, the target letter is the previous letter from the series (immediate repetition, e.g. “R, R “). In the 2-back condition, the target letter is the one presented 2 trials back (a repeated letter separated by another letter, e.g. “ R, A, R “).

**Fig. 1 Fig1:**
[figure not shown]
fMRI letter-n-back task: conditions and experimental design. 1. Explanation of the 3 conditions. The arrow indicates the target letter. 2. Schematic representation of the response pad used during training and MRI indicating the buttons to push for target and non-target letters. 3. Design of the 3 runs used during the task. 4. Description of the event sequence during a 1-back block. Other conditions follow the same timing

The task will include 3 runs of 9 blocks composed of 14 letters (3 target and 11 non-target letters; 9 blocks of each condition; total duration: 15–20 min). The first 2 runs will follow a fixed order in the block presentation, whereas the last run follows a randomized block order (conditions/blocks will alternate). Instructions on the type of block (0-, 1- or 2-back condition) are presented on the screen before each block. Presentation will start when the patient is ready (he/she will push a button). Within a block, each letter is presented for 1.2 s, followed by a 1.2 s fixation cross (interstimulus interval) until the next letter appears. The patient can respond during the full 2.4 s of letter and fixation cross presentation. Stimulus presentation and interstimulus interval durations were selected upon pilot experiment results in healthy elderly and MCI patients.

## Statistical analysis plan and sample size calculation

### Basic statistical analyses

First we will use linear mixed model equations (lme) using the open-source software R [144] to evaluate the longitudinal effects for all variables separately comparing both experimental groups to the control group and to each other. These lme are flexible and powerful statistical models that consider several levels of clustering, continuous, ordinal and categorical explanatory variables. They support unbalanced data and allow to integrate demographic data into the models. Our 2 patient groups may turn out unbalanced due to attrition. Moreover, because we are interested in development, we will incorporate the baseline scores in the models. This will allow correcting for differences between the groups at baseline.

We will also compare those results with more traditional multivariate analyses of covariance.

If the data are not normally distributed, and if data transformation cannot cope with this non-normality, we will either use robust analyses (weighting outliers or other influential observations) or use non-parametric approaches.

In testing multiple contrasts, adjustments of the alpha criterion for multiple comparisons will be applied.

Concerning the primary objective, the analysis will consist in evaluating increase or less decrease (experimental group 1 or 2 vs. the control group) of the total weighted score at the COGTEL test [79, 80] at t1 and t2 compared to baseline and to the passive control group, by means of lme and MANCOVA analyses, using a two-sided alpha criterion of 0.05.

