Concerning brain plasticity, 2 recent RCT trials used structural and functional Magnetic Resonance Imaging (MRI) to assess the efficacy of treatments on MCI patients [68, 69]. Simon and colleagues [68] compared mnemonic strategy training over 2 weeks to an active control group of MCI patients who followed an educational program. Neuropsychological tests and functional MRI (fMRI), the latter using a Face-Name Recognition Task, were measured before and after training. MCI patients in the training group showed improved face-name memory and higher fMRI activation in the left anterior temporal lobe. No indication of far transfer occurred. The experimental group's face-name memory task demonstrated preserved improvement after one and three months. The "Train the Brain" consortium [69] compared the effects of combined 7-month physical-cognitive training to a passive control group on cognitive decline, gray matter volume, cerebral blood flow (CBF) in hippocampal areas, and fMRI activity elicited by a cognitive task. Cognitive status significantly improved in the training group whereas it decreased in the control group. In the training group, parahippocampal CBF increased. Both studies [68, 69] show that non-pharmacological interventions may improve cognitive functioning and brain health in MCI patients.

Mild Cognitive Impairment (MCI) represents a cognitive state between normal aging and dementia, with a minor age-related loss of cognitive ability that does not importantly impact daily life functioning. Symptoms most frequently involve impairments in memory, attention, spatial orientation, executive functions [70–72]. Increased fall risk is an associated condition [61].

Although some MCI patients may stay stable or even recover to some extent [73], some of them are on a downward slope to overt dementia, i.e., a pathway of no return [73, 74].

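### If one variance is pooled over MCI patients and healthy controls, the false-positive rate of the only randomised contrast (music versus psychomotor) depends on how variable the controls are; estimate that contrast from patients only

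*Protocol article*

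**What the plan says.** All points are from the protocol article.

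- **Model.** Basic statistical analyses plans linear mixed models in R "to evaluate the longitudinal effects for all variables separately comparing both experimental groups to the control group and to each other". The section Comparisons lists the same contrasts: each patient group against the healthy group, and the two patient groups against each other.
- **Primary objective.** "the analysis will consist in evaluating increase or less decrease (experimental group 1 or 2 vs. the control group") on the weighted COGTEL score, "by means of lme and MANCOVA analyses, using a two-sided alpha criterion of 0.05".
- **Multiplicity.** "In testing multiple contrasts, adjustments of the alpha criterion for multiple comparisons will be applied"; no method is named.
- **Fallback.** Transformation, robust or non-parametric methods are foreseen if the data are not normal. Nothing is foreseen for unequal variances.
- **Randomisation.** "Blocked randomization is applied to the experimental groups only" (Study design). The third group consists of "healthy controls (n ~ 16) that are not part of the randomization process".
- **Course of MCI.** The background states that some patients stay stable or partly recover, while "some of them are on a downward slope to overt dementia". No SD of COGTEL change is given for patients or controls.

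**The concern.** Music versus psychomotor is the only comparison that randomisation protects, and it carries the stated expectation that music will have much the stronger effect (Main hypothesis). If all three groups share one residual variance, the standard error of this contrast is computed partly from healthy people who received no intervention and were not randomised.

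The two populations may well differ in how much individuals change. The mixed course of MCI described in the background makes more variable change in patients plausible, and only patients can vary in their response to an intervention. If patients do vary more, the pooled standard error is too small for the randomised contrast, its interval too narrow and its p-value too small. If controls vary more, the opposite happens and power is lost. Either way, the error rate of the randomised test depends on a group outside that comparison.

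**Working it through.** The plan prints no figure that depends on this choice, so there is none to reproduce.

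**Inputs**
- Group sizes (Attrition / Drop-outs): 16/16/16 planned; 12/12/16 if each patient arm falls to its minimum and the control target is kept.
- Two-sided alpha of 0.05 (Basic statistical analyses).
- r = control SD / patient SD. The documents do not give it, so it is **assumed** and varied on both sides of 1.

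**Step 1: share of the error degrees of freedom.** Controls supply 16 - 1 = 15. The total is 48 - 3 = 45 with 16/16/16 (15/45 = 33%) and 40 - 3 = 37 with 12/12/16 (15/37 = 41%). Patients alone supply 30 or 22.

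**Step 2: bias of the standard error.** With patient variance 1 and control variance r², the pooled SE as a fraction of the correct SE for music versus psychomotor is

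k = sqrt[(df_patients + 15 r²) / df_total].

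At r = 0.5:
- 16/16/16: sqrt[(30 + 3.75)/45] = sqrt(0.75) = 0.866, so the SE is 13% too small.
- 12/12/16: sqrt[(22 + 3.75)/37] = 0.834, so the SE is 17% too small.

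**Step 3: type I error at nominal 5%** (400,000 simulated draws per setting, common variance):

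| r | k, 16/16/16 | type I error | k, 12/12/16 | type I error |
|---|---|---|---|---|
| 0.5 | 0.866 | 9.1% | 0.834 | 10.2% |
| 0.75 | 0.924 | 6.9% | 0.907 | 7.5% |
| 0.9 | 0.968 | 5.8% | 0.961 | 5.9% |
| 1.0 | 1.000 | 5.0% | 1.000 | 5.0% |
| 1.25 | 1.090 | 3.4% | 1.108 | 3.1% |

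Analytic check at r = 0.5, 16/16/16: the effective critical value is 2.014 × 0.866 = 1.744. The Satterthwaite degrees of freedom are (30 + 3.75)² / (30 + 0.0625 × 15) = 36.8. The two-sided tail area beyond 1.744 is then 9.0%, in line with the simulation.

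**Step 4: a model closer to the plan.** A random-intercept, baseline-adjusted analysis of two follow-up visits (6,000 simulated trials per setting) gives 8.9% and 9.4% at r = 0.5, 7.0% and 8.0% at 0.75, 4.9% and 5.6% at 1.0, and 3.3% and 3.1% at 1.25. The pattern is not an artefact of using simple change scores.

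**Step 5: the primary contrasts.** Under the same pooled variance at r = 0.5, the test of one patient arm against controls rejects in 3.4% (16/16/16) and 4.9% (12/12/16). It is not inflated.

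**Step 6: the promised alpha adjustment.** If this were Bonferroni over three contrasts (an assumption), the nominal level would be 0.05/3 = 1.67%. At r = 0.5 the actual level would be 3.8% (16/16/16) or 4.5% (12/12/16). Adjustment does not remove the problem.

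**Step 7: patients only.** With the variance taken from the randomised patients alone, the simulated type I error in the Step 3 setting is 5.0-5.1% at every r and both sets of group sizes.

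**The case against.** The strongest reply is that neither premise is written down. The article does not say that all contrasts come from a single fit, and it does not fix a common variance. Mixed models in R can take group-specific variances, and that detail is commonly left to an analysis plan, which is not shown here. This stands, and it is why the point is conditional. What remains is that the three-group reading is the natural one, that standard MANCOVA does assume a common covariance matrix, and that the article provides a fallback for one assumption failure only.

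A reader might also infer more than the documents support:

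- **That the plan itself says healthy controls vary less.** It does not. The expectation under Secondary hypotheses that controls stay stable or regress describes their mean course, not their spread. The account of mixed MCI courses is qualitative background.
- **That wave 1 demonstrates the larger patient variance.** Of the 14 who consented, there were "2 who went into early dementia", but both stopped participating. Withdrawal and discontinuation excludes the data of patients who withdraw, so these two would add nothing to the analysed variance.
- **That the randomised test is certainly anti-conservative.** At r = 1 the level is correct, and at r = 1.25 the test is conservative. No document figure excludes either case.
- **That the primary result is at risk of a false positive through this route.** The primary objective compares each patient arm with controls, and those tests are not inflated when controls vary less.

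**Conclusion.** The point holds in conditional form. If variance is pooled over the three groups, the type I error of music versus psychomotor is set partly by the variability of a healthy group outside that comparison. It runs from about 9-10% at a control/patient SD ratio of 0.5, through 5% at 1.0, to about 3% at 1.25. This rests on two assumptions that the documents neither state nor exclude: a joint fit with a common variance, and an SD ratio different from 1. A ratio below 1 is plausible but not shown. The point concerns the randomised contrast, not the stated primary tests. It is worth acting on because the remedy works whatever the ratio turns out to be and costs very little.

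**What to change.** - Estimate music versus psychomotor, for the primary and the secondary outcomes, from a mixed model fitted to the randomised patients only. Do the same for the accompanying MANCOVA.
- For the contrasts with healthy controls, state that patients and controls have separate residual variances (for example varIdent by diagnosis in nlme). This part was not simulated. With 12 to 16 people per group, the model should be kept simple.

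**Cost.** No new data and about one line of code per model. For the randomised contrast, error degrees of freedom fall from 45 to 30 with 16/16/16 (critical t 2.01 to 2.04), or from 37 to 22 with 12/12/16 (2.03 to 2.07). With equal variances that widens the interval by about 1% (2.042/2.014) or 2% (2.074/2.026).
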